## Abstract

**Background:**

Nationwide, emergency response systems depend on 9-1-1 telecommunicators to prioritize, triage, and dispatch assistance to those in distress. 9-1-1 call center telecommunicators (TCs) are challenged by acute and chronic workplace stressors: tense interactions with citizen callers in crisis; overtime; shift-work; ever-changing technologies; and negative work culture, including co-worker conflict. This workforce is also subject to routine exposures to secondary traumatization while handling calls involving emergency situations and while making time urgent, high stake decisions over the phone. Our study aims to test the effectiveness of a multi-part intervention to reduce stress in 9-1-1 TCs through an online mindfulness training and a toolkit containing workplace stressor reduction resources.

**Methods/design:**

The study employs a randomized controlled trial design with three data collection points. The multi-part intervention includes an individual-level online mindfulness training and a call center-level organizational stress reduction toolkit. 160 TCs will be recruited from 9-1-1 call centers, complete a baseline survey at enrollment, and are randomly assigned to an intervention or a control group. Intervention group participants will start a 7-week online mindfulness training developed in-house and tailored to 9-1-1 TCs and their call center environment; control participants will be “waitlisted” and start the training after the study period ends. Following the intervention group’s completion of the mindfulness training, all participants complete a second survey. Next, the online toolkit with call-center wide stress reduction resources is made available to managers of all participating call centers. After 3 months, a third survey will be completed by all participants. The primary outcome is 9-1-1 TCs’ self-reported symptoms of stress at three time points as measured by the C-SOSI (Calgary Symptoms of Stress Inventory). Secondary outcomes will include: perceptions of social work environment (measured by metrics of social support and network conflict); mindfulness; and perceptions of social work environment and mindfulness as mediators of stress reduction.

**Discussion:**

This study will evaluate the effectiveness of an online mindfulness training and call center-wide stress reduction toolkit in reducing self-reported stress in 9-1-1 TCs. The results of this study will add to the growing body of research on worksite stress reduction programs.

**Trial registration:**

ClinicalTrials.gov Registration Number: NCT02961621 Registered on November 7, 2016 (retrospectively registered).

## Background

The effectiveness and efficiency of an emergency response system depends on 9-1-1 telecommunicators (TCs), the emergency call receivers and dispatchers who are the *first* first-responders to assist people in distress. 9-1-1 TCs prioritize and triage incoming calls delivered via myriad channels (cell and landline phone; TTY for deaf-and-hard-of-hearing citizens); collect and distill call information; dispatch police, firefighters, emergency medical technicians, and paramedics; and may issue medical and other instructions to callers while they await the assistance dispatched to the scene. Each 9-1-1 TC fields thousands of calls every year, ranging from trivial to life-threatening, while simultaneously monitoring and entering data into up to six different computer screen displays in real time during each call.

Much of the research on stress in first responders has been focused on police and firefighters, and the relationship between their trauma exposures and post-traumatic stress disorder (PTSD) [1, 2]. Although it is known that vicarious or secondary exposure can create secondary traumatic stress (i.e., behaviors and emotions resulting from knowledge about a traumatizing event that was experienced by another person and the desire to help that person) [3, 4] or compassion fatigue (i.e., cumulative stress) [4–7] in first responders, few studies have focused specifically on the occupational stressors and work-related stress symptoms of 9-1-1 TCs. Troxell (2008), one of the first to study 9-1-1 TCs, reported high peritraumatic distress (i.e., responses occurring at the time of a trauma and immediately after) and a positive relationship between peritraumatic distress and compassion fatigue in 9-1-1 TCs [8]. Pierce and Lilly (2012) added to these findings by assessing traumatic call exposure, peritraumatic distress, and PTSD symptoms in 9-1-1 TCs, reporting high levels of peritraumatic distress and a moderate, positive relationship between peritraumatic distress and PTSD symptom severity. This research suggests that direct, physical “incident scene” exposure(s) to traumata may not be necessary to cause or to increase risk for PTSD in 9-1-1 TCs [9].

The adverse outcomes associated with exposure to acute and chronic occupational stressors are costly and include physical and mental diseases, and impaired work performance, which can threaten the attainment of an organization’s critical mission(s) [10]. In addition to trauma exposures, 9-1-1 TCs are subject to those stressors commonly encountered by non-emergency call center workforces, including: fast-paced and time-urgent decision-making; tense interactions with distressed and sometimes abusive callers; time pressure to meet call processing requirements; and a negative work culture, which can include co-worker conflict, and a lack of appreciation or recognition from supervisors [11, 12]. Rameshbabu et al. (2013) reported that rotating shifts, common in 9-1-1 TCs, and their accompanying inadequate sleep were negatively associated with physical health outcomes in call center personnel [13]. Long hours of sedentary, high mental demand computer work, also ubiquitous in TCs, have been found to increase the risk for musculoskeletal symptoms [14] which can also be associated with psychological distress [15, 16]. Workplace environmental conditions such as lighting, ventilation, temperature, break/lunch room availability, and workstation ergonomics have also been found to exacerbate work-related stress in TC workforces [11, 12]. In addition, frequent technology updates including incremental and major “upgrades” in technologies, also common in the TC workplace, can cause “technostress” which has been shown in other worker groups to be associated with decreased job satisfaction and declines in productivity, commitment to the organization, and intention to remain on the job. [17]

### Project aims

The objective of this study is to develop and test the effectiveness of an evidence-based, multi-level intervention program designed to reduce stress in 9-1-1 TCs. The project’s primary aim is to:develop, implement, and test the effectiveness of an individual-level online mindfulness training to reduce stress in 9-1-1 telecommunicators.

The secondary aims are to:develop and test the effectiveness of an organizational-level online worksite stress reduction toolkit utilized by 9-1-1 TC managers that is designed to reduce or minimize sources of stress in the 9-1-1 call center environment.test if the multi-level intervention program will lead to increases in TCs’ positive perceptions of the call center social work environment.test if participation in the mindfulness training increases mindfulness.test if increases in TC’s positive perceptions of the call center social work environment and increases in mindfulness serve as mediators of stress reduction in 9-1-1 TCs.

### Conceptual framework

Borrowing from the literature on occupational stress, individual stress, and coping response we developed a conceptual framework that describes how this multilevel intervention is expected to effect stress in 9-1-1 telecommunicators (Fig. 1). At the individual level, mindfulness training is hypothesized to increase an individual’s ability to regulate their emotional response to stressors, whereas the call center manager-directed organizational level intervention is hypothesized to reduce worksite stressors and increase perceived social support by implementation of targeted strategies and worksite policies.

**Fig. 1 Fig1:**
[figure not shown]
Conceptual Framework

### Mindfulness and stress

While there is no universally agreed upon definition, mindfulness can be defined as the individual’s ability to pay attention to and be aware of present moment experience, closely observe and describe sensations, perceptions, thoughts, and feelings, and act with full awareness [18]. A growing literature base has established the salutary effects of mindfulness-based interventions (MBIs). MBIs model, teach and cultivate the inner attentional resources of a trainee with the goal of learning to recognize and accept stress responses. Through recognition and acceptance, individuals learn to no longer rely on avoidance or suppression of emotional responses. Avoidance and suppression of emotional responses have been connected to greater stress levels and psychopathology following exposure to distressing events [19–23]. Mindfulness has been reported to be positively correlated with compassion satisfaction [24, 25] and inversely correlated with compassion fatigue [26–28] and burnout [29–31]. Mindfulness has also been associated with reduced stress in firefighters and paramedics [32] and MBIs have also been associated with fewer PTSD symptoms in combat veterans [33–38]. Specific to 9-1-1 TCs, a recent cross sectional/non-intervention study showed that increased mindfulness was inversely correlated with self-reported symptoms of stress [39]. And regarding delivery of mindfulness training, *online* MBIs have been shown to be effective in a number of workplace settings [40–46].

### Worksite environment and stress

In occupations such as the 9-1-1 TCs’, in which work demands are high and worker control is low, employee wellness and stress-mediated outcomes can impact attrition, turnover, burnout/exhaustion and absenteeism [47, 48]. Worksite characteristics affect employees’ productivity, satisfaction, and stress; however, an array of interventions may improve the quality of the work environment, and worksite health promotion activities can support employees’ healthy behaviors. The role of managers in particular, as a resource and support to employees has been highlighted as a significant component of organizational-level interventions that can reduce or mitigate stress [49–51]. In addition, interpersonal conflict between employees is a stressor amenable to intervention, for example, by training supervisors to adopt strategies for conflict management [52] and assisting organizations in adoption of anti-bullying policies [53]. Other known strategies for promoting organization-level wellness include healthy nutrition and exercise programs [54] and the reduction or elimination of environmental hazards in the workplace [11]. Thus, an array of interventions have been documented to improve the quality of the work environment, reduce symptoms of stress, and improve worker health- but the vast majority of this research has been conducted with non-9-1-1 TC workers.

## Methods/design

### Study design

The study is a longitudinal multi-stage study design that consists of a randomized controlled trial to evaluate the effectiveness of an online mindfulness training in reducing symptoms of stress in 9-1-1 call-center TCs, followed by 3 months access to an online call center stress reduction activity toolkit for the call center managers. We will recruit TCs from multiple enrolled 9-1-1 call centers nationwide. As shown in Fig. 2, at enrollment, TCs will complete a baseline stress survey and will then be randomized to either a mindfulness training intervention or wait-list control group. Following the mindfulness training, both the intervention and control groups will complete a post-training survey. Next, managers from all participating call centers will be provided access to the online Toolkit. After three months of access, all 9-1-1 TCs (training and control groups) will be asked to complete a post-toolkit survey.

**Fig. 2 Fig2:**
[figure not shown]
Study Design

### Population and procedures

The study population consists of 9-1-1 TCs working in multiple 9-1-1 call centers serving urban, suburban and rural areas in the United States. All participating call centers respond to 9-1-1 calls for fire, medical or police emergencies, with many centers responding to all three emergency call types.

Recruitment will be conducted in two stages. First, the study team will conduct an outreach campaign to 9-1-1 call centers, using industry publications and listserv announcements, to enroll call centers into the study. Next, at enrolled call centers, 9-1-1 TCs will be recruited through staff announcements, recruitment flyers, email, and word-of-mouth. After obtaining electronic informed consent, participants will be asked to provide demographic (age range, gender) and other information (length of employment, etc.) and complete the baseline survey. All participant information is stored on computers.

### Randomization

Respondents from each enrolled call center who are eligible, have provided their informed consent, and have completed the baseline survey, will be randomized into either the mindfulness training group or wait-list control group.

### Description, Design & Development of Interventions

#### Individual-level mindfulness training

The online mindfulness training is composed of seven modules to be completed weekly, over a 7-week time period. Each weekly online module is expected to require participants between 20 to 30 min to complete. Each individual module consists of the following components:A short video introducing the theme for the weekA few paragraphs describing the theme and activities for the weekAn audio-guided meditative stress reduction exerciseSuggestions for brief mindfulness activities that can be performed throughout the dayA brief check-in form for participants to let study staff know how the training is goingA moderated discussion board on which participants can post questions/comments if they wish

The mindfulness training is developed by clinicians and investigators who are trained mindfulness teachers and practitioners. The training is adapted from the widely-used Mindfulness-Based Stress Reduction (MBSR) program, an evidence-based training program originally implemented as in-person training [55, 56]. For our project, the MBSR training content was modified, abbreviated, and revised to accommodate an online format and tailored to meet the constraints and needs of the 9-1-1 TC population.

#### Organizational-level stress reduction toolkit

The online Toolkit is comprised of several modules providing evidence-based and expert-informed content and strategies for call center managers to consider and implement in an effort to reduce select stressors and increase network support in their worksites. The specific topics were selected based upon consultations and guidance from our research program advisory board consisting of call center managers from throughout our catchment area. The on-line toolkit includes modules focused on the following content areas: Conflict management; Bullying in the Workplace; and Reducing Technostress; with additional resources on Health and Wellness. Content is specifically tailored for managers and for their utility in 9-1-1 call centers.

### Procedures

#### Implementation protocols

After completing the baseline survey, participants will be assigned a study ID number and are randomized to either start the online mindfulness training (the intervention group) or are assigned to the wait-list control group.

Two weeks following the end of the online mindfulness training all participants will be asked to complete the second survey. Two weeks following the end of the call-center-level toolkit availability, all participants will be asked to complete the third survey.

#### Online mindfulness training

During the 7-week training period, the intervention group will be contacted each week, receiving two emails: one containing the link to that week’s training module and one providing additional suggestions for incorporating that week’s stress reduction activities into daily living. Participants will be encouraged to complete the training on a designated weekday to allow approximately 7 days between each module. Participants will also be encouraged to practice the mindfulness skills introduced in the module throughout the week for approximately 10 min every day.

#### Online stress reduction toolkit

Following the intervention group participants’ completion of the mindfulness training and completion of the second survey, managers of all participating call centers will be provided with a link to access the Toolkit and are asked to share the link with other administrative personnel at their call center who may be in a position to implement any of the suggested activities. Managers will have access to the Toolkit for 3 months and will receive bi-monthly emails encouraging them to use the Toolkit content and directing them to specific modules of the Toolkit. After 3 months access to the Toolkit, all participants complete the third survey.

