#### Secondary analyses

The secondary outcomes examined will include mindfulness and perceptions of social work environment. We anticipate conducting the following analyses:*Effect of the intervention on mindfulness*: We will examine the effect of the intervention on mindfulness score using the same model as the primary analysis with MAAS score as the outcome.*Effect of intervention on perceptions of social work environment*: We will examine the effect of the intervention on perceptions of social work environment (social support and network conflict) using the same model as the primary analysis with the 4 VAS.*Analysis of mindfulness and perceptions of social work environments as mediators of stress reduction*: We will conduct analyses of the mediation effect of mindfulness (MAAS measures) and perceptions of social work environments (workplace social support and conflict VAS measures) on the intervention, estimating the direct and indirect causal effects using the approach of Imai [73].*Effect of training participation on stress:* Training participation will be examined using two measures: number of trainings completed as measured by access logs for viewing training videos and self-report mean number of days per week on which mindfulness was practiced. The effects of level of participation will be examined using repeated measures mixed effects models, with the effect of participation level assessed by interaction terms between level of participation and follow-up time. The models will include level of participation as a covariate, fixed effect for time (3 levels; baseline, post intervention and follow up), site, time–by-level-of-participation interaction and a random intercept for participant.*Effect of online Toolkit*: A secondary aim of this study is to determine the extent to which an online Toolkit for reducing occupational stress in call centers improves call center climate four months post implementation of the Toolkit. We will use a multi-level model to examine the effects of implementation of the toolkit (as measured through the manager survey) on mean call center stress levels and call center climate, as measured by workplace support and conflict measures.

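### The toolkit goes to every call center at the same step, so its effectiveness aim rests on a self-selected, non-randomized comparison of reported implementation

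*Protocol article*

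**What the plan says.** Under Project aims, the protocol article sets as its first secondary aim to "develop and test the effectiveness of an organizational-level online worksite stress reduction toolkit utilized by 9-1-1 TC managers". A further aim concerns whether the combined multi-level program improves perceptions of the social work environment.

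Under Randomization, individual respondents "will be randomized into either the mindfulness training group or wait-list control group". No other unit is randomized. Under Study design, once the post-training survey is done, "managers from all participating call centers will be provided access to the online Toolkit", and the Online stress reduction toolkit section repeats that "managers of all participating call centers will be provided with a link to access the Toolkit". Use is voluntary: the content offers "strategies for call center managers to consider and implement in an effort to reduce select stressors", supported by reminder emails.

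Two analyses involve the toolkit. The model under Primary analyses has a term for toolkit implementation crossed with the third time point. Under Secondary analyses, a multi-level model is to "examine the effects of implementation of the toolkit (as measured through the manager survey) on mean call center stress levels and call center climate", and the stated purpose is to learn how far the toolkit improves call center climate.

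**The concern.** The aim is causal, but the design provides no randomized or concurrent toolkit-free group. The wait-list arm cannot serve as one, because its members work in centers that also receive the toolkit. For the same reason the combined program is never compared with its absence: both arms have the toolkit by the third survey, so randomization isolates the training alone.

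The plan therefore relies on differences between managers in what they chose to implement. A manager may act because stress has just spiked, or because the center is already improving and has capacity to spare. In either case implementing centers would improve more between surveys even if the toolkit did nothing. The trial could then report as toolkit effectiveness what is only an association.

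**Working it through.** **1. The stated sample size does not cover this aim.** For an effect size of 0.5, 5% two-sided (sidedness assumed) and 80% power, the two-sample t-test needs 64 per group, and power at 65 is 80.8%. With 18% loss, 130 / (1 − 0.18) = 159, against 160 stated. The figures reproduce, but they concern the training comparison. No size is given for the toolkit aim, and the number of centers is not stated.

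**2. What the toolkit term can estimate.** Take 16 centers (assumed). The fixed effects under Primary analyses give 1 (intercept) + 1 (group) + 2 (time) + 2 (group by time) + 15 (site) + 1 (toolkit at time 3) = 22 columns.
- Coded as access, the toolkit term equals 1 for everyone at time 3. It duplicates the time-3 column, the rank is 21, and the term cannot be estimated.
- Coded as implementation, with half the centers implementing, the rank is 22.

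The term is estimable only through variation that managers chose.

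**3. What cancels.** A shift shared by all centers drops out of implementers minus non-implementers. Adding a common −0.3 SD shift at the third survey left the contrast unchanged in simulation. Stable center differences drop out of any change score and are absorbed by the site effects.

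**4. What does not cancel.** Assume no toolkit effect, a temporary center-wide component with variance share v at each survey, and implementation split at the median of a propensity that correlates r with the center's component at the second survey. Implementers then exceed non-implementers at that survey by

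2 × √(2/π) × r × √v = 1.596 × r × √v.

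The excess is gone by the third survey and looks like benefit. Averaging baseline with the second survey halves it. That average is the comparator implied by the third-time-point term.

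| Assumed r, v | Against survey 2 alone | Against average of baseline and survey 2 |
|---|---|---|
| 0.3, 0.03 | 1.596 × 0.3 × 0.173 = 0.083 SD | 0.041 SD |
| 0.5, 0.10 | 1.596 × 0.5 × 0.316 = 0.252 SD | 0.126 SD |

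Simulations on this grid (16 and 32 centers, 130 telecommunicators, within-person correlation 0.6, stable center ICC 0.10) agree, with largest values of about 0.26 and 0.13. Testing center means, the false-positive rate is about 6 to 21% against survey 2 alone and about 5 to 10% against the average. It is 5% when implementation is unrelated to the center's course.

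For scale, 15 C-SOSI points at an effect size of 0.5 or 0.4 implies an SD of 30 or 37.5. Then 0.04 to 0.13 SD is about 1.2 to 4.9 points, and 0.08 to 0.25 SD is about 2.4 to 9.4 points. The conversion is rough, because the protocol's effect size refers to the pre-post difference.

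**5. A second scenario.** Suppose instead that centers already improving are more likely to implement (10 to 26 centers, SD of center-level change 0.2 to 0.5, all assumed). The spurious benefit is then about 0.16 to 0.61 SD, with false positives of 11 to 68%. The assumptions are stronger, since the center's own trend drives implementation directly.

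**6. What randomized release could detect.** With 130 telecommunicators in K centers, m = 130/K, design effect DE = 1 + (m − 1) × ICC, and t quantiles on K − 2 degrees of freedom, the detectable effect at 80% power is (t₀.₉₇₅ + t₀.₈₀) × √(4 × DE / 130).
- K = 32, ICC 0.02: (2.042 + 0.854) × √(4 × 1.061 / 130) = 0.52 SD of change.
- K = 16, ICC 0.10: (2.145 + 0.868) × √(4 × 1.712 / 130) = 0.69 SD of change.

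**The case against.** The strongest reply is that the plan does contain a comparison, with two surveys before the toolkit and a site effect in the model. That stands, and it limits what can be said. A reader might infer that a secular trend, or simply better managers implementing more, would pass for a toolkit effect. Step 3 shows otherwise: a common trend would bias only a plain before-after analysis, which the article does not plan, and stable manager quality cancels in change. A reader might also infer that one person reports both exposure and outcome. The documents do not support that: managers pass the link to other administrative staff, and stress and climate are reported by telecommunicators.

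The Covariates section also has managers report any unusual organization-wide stressful event during the study and lists this among possible confounders. It bears directly on the bad-spell scenario. But the article does not commit it to the toolkit model, and one such item cannot capture staffing changes or a center already on the mend.

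The full analysis plan may add adjustment. It cannot add an unexposed group, because universal release is a stated feature of the design.

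Finally, this is a secondary aim. The reading that it undermines the primary result is not supported: the toolkit opens after the second survey, and telecommunicators are randomized from each enrolled center.

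**Conclusion.** The point holds in this form: the toolkit has no randomized or concurrent toolkit-free comparison, and its estimated effect depends on self-selected implementation. Effectiveness wording for the toolkit, or for the combined program, goes beyond what the design can show.

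The size is uncertain. In the bad-spell scenario the spurious benefit is modest under the comparator that the primary model implies (0.04 to 0.13 SD) and about double if only the second survey is used. The article does not say which comparator the secondary multi-level model uses. These figures illustrate a mechanism on assumed inputs: the number of centers, the temporary center variance and the strength of selection are not in the document. They are not a forecast of the bias in this trial.

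**What to change.** Restate the toolkit aim under Project aims and the toolkit paragraph under Secondary analyses. The analysis should estimate a non-randomized association between manager-reported implementation and change in center stress and climate, adjusted for center levels at both earlier surveys and for the manager-reported stress event. State that no effectiveness claim will be made from it for the toolkit or for the combined multi-level program. The cost is wording and a weaker claim. The adjustment uses data already planned and reduces the bias without removing it.

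An option, only if the links are not yet out: randomize centers to toolkit release after the second or after the third survey, and compare by assigned release with a center random effect. Implementation then becomes descriptive. This needs an amendment but no extra participants or surveys. About half the centers would wait roughly three more months. The amendment should state that such a comparison would detect only about 0.52 to 0.69 SD (16 to 32 centers assumed). That lies above the protocol's meaningful range of 0.4 to 0.5, even before dilution from voluntary uptake. Registration was retrospective, so this option may already have passed.
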